#### Acceptance

Acceptance is defined as participants’ subjective evaluation of the iEXPECT intervention (outcome criterion 3). This includes perceived enjoyableness, usefulness and the intervention’s relevance to their daily social functioning. Ratings are gathered through self-report at the end of each module and via a standardised satisfaction questionnaire (CSQ-I)^27^ after intervention completion (T1) and at 6-month follow-up (T3). Together, these outcomes will inform the practicality and perceived value of the intervention from the patient’s perspective and provide critical insight for the planning of a future full-scale efficacy trial.

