### Data analysis plan

The hypotheses of primary interest refer to the feasibility of the study design and acceptability of the iEXPECT intervention as an internet-based intervention, which will be assessed based on three criteria:

Feasibility of the study design is assumed if at least one participant per week per centre can be recruited (approximately 160 participants from three centres over 53 weeks), and >49% of all randomised patients provide complete data for the 6-month follow-up assessments, including biomarkers. The recruitment threshold of ≥1 participant per centre per week was based on the assumption that a Phase III trial with *X* centres could achieve its enrolment target within a recruitment period of *Y* under this rate. The ≥49% randomisation threshold was chosen to reflect an acceptable screening-to-randomisation efficiency while accounting for expected attrition. The proportion of patients with complete data for the 6-month follow-up assessments (including biomarkers) will be reported as a point estimate per group. Two-sided 95% CIs will be given.Feasibility of the internet-based intervention is assumed if >75% of the randomised patients in each iEXPECT arm complete at least 1 (>0) online module before the surgery. The completion rate will be reported as a point estimate per intervention group, and two-sided 95% CIs will be provided. To assess whether time to surgery influences outcome criterion 2 (completion of at least one online module before surgery), a sensitivity analysis will be considered.Acceptance will be assessed by self-report ratings at the end of each online module and with the CSQ-I after the intervention (T1) and the 6 months follow-up (T3). To evaluate a session’s/the intervention’s enjoyableness, usefulness and effect on daily social functioning using a 5-point scale (1=fully disagree, 2=disagree, 3=not sure, 4=agree, 5=fully agree; examples for items: ‘This session/intervention was useful and sensible’, ‘I would recommend this session/intervention to others’, ‘This session/intervention lived up to my expectations’). Acceptance of the internet-based intervention is assumed if the mean rating for overall acceptance/satisfaction with the intervention (calculated after completion of each of the four modules) exceeds 3.4. This threshold was chosen to reflect a tendency toward agreement rather than neutrality (>3=‘not sure’) and is supported by prior data^12^ suggesting an expected mean of 3.7 (SEM=0.14), making >3.4 a conservative and statistically robust criterion. Each intervention group will be analysed separately and mean rating of acceptance/satisfaction with the intervention will be presented for each online module. An overall mean rating across the four modules/predefined timepoints of assessment will be calculated.

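### The acceptance rule (mean >3.4) fixes neither denominator nor weighting for its across-module mean, so if early stopping goes with dissatisfaction it can pass when the mean counting each patient once does not

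*Protocol article*

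**What the plan says.** The Acceptance section of the protocol article makes acceptance a primary outcome. It states "Ratings are gathered through self-report at the end of each module", and adds the CSQ-I at T1 and T3.

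Under criterion 3 of the Data analysis plan, items are scored "1=fully disagree, 2=disagree, 3=not sure, 4=agree, 5=fully agree". Acceptance is assumed if "the mean rating for overall acceptance/satisfaction with the intervention (calculated after completion of each of the four modules) exceeds 3.4". For reporting, the text says "Each intervention group will be analysed separately and mean rating of acceptance/satisfaction with the intervention will be presented for each online module", followed by "An overall mean rating across the four modules/predefined timepoints of assessment will be calculated".

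Three further features of the article matter here:

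- Criterion 2 and the retention part of criterion 1 are expressed as shares of randomised patients. Criterion 3 names no denominator.
- Criterion 2 is met by one completed module. The note to Table 1 treats modules 1–3 as the minimum before surgery. No primary criterion sets a floor on completion of modules 2 to 4.
- The CSQ-I belongs to the acceptance definition but has no threshold.

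**The concern.** A patient who stops after module 1 leaves one rating, and a patient who finishes leaves four. Unless the plan says otherwise, an average across modules gives the finisher more influence on the result. If finishers are on the whole the more satisfied patients, the average moves towards acceptance, and it moves further as more dissatisfied patients stop.

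This matters because the mean is compared with a fixed cut-off for a primary outcome that informs the planning of a Phase III trial. The same set of ratings can pass or fail depending on a weighting that the article does not state. Criterion 2 would not reveal the problem, since a patient who stops after module 1 counts as engaged.

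**Working it through.** **The plan's own figures.** Sample size per intervention arm (Sample size and study power): n = 1.96² × 0.84 × 0.16 / (0.84 − 0.75)² = 63.74, rounded up to 64, as stated. Rationale for 3.4 (expected mean 3.7, SEM 0.14): 3.7 − 1.96 × 0.14 = 3.43, just above 3.4. Both reproduce. The margin between expected mean and cut-off is 3.7 − 3.4 = 0.3.

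**Inputs.** From the article: four modules, cut-off 3.4, 64 patients per arm, more than 75% required and 84% expected to complete at least one module. Assumed, because the article gives no figures: the ratings and the share who stop.

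**Formulas.** Let a share s of starters rate b and stop after module 1, while the rest rate a on all four modules.

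- Each patient counted once: P = (1 − s)a + s·b. This is also the module 1 mean.
- Mean of the four module means: M = (P + 3a)/4.
- All ratings pooled: R = [4(1 − s)a + s·b] / [4(1 − s) + s].

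M exceeds P by 0.75 × s × (a − b), which is above zero whenever those who stop rate lower than those who finish.

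**Main example.** 52 of 64 start (81%, so criterion 2 is met); 26 finish and rate 4.0; 26 rate 2.6 and stop after module 1.

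- P = (26 × 4.0 + 26 × 2.6)/52 = 171.6/52 = 3.30: fails.
- M = (3.30 + 4.0 + 4.0 + 4.0)/4 = 3.825: passes.
- R = (171.6 + 78 × 4.0)/(52 + 78) = 483.6/130 = 3.72: passes.

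**Other assumed inputs, same formulas.**

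| Finishers | Stop after module 1 | Module means | Pooled | Per patient |
|---|---|---|---|---|
| 36 rating 3.7 | 18 rating 2.5 | 3.60 | 3.57 | 3.30 |
| 30 rating 4.0 | 22 rating 2.8 | 3.87 | 3.81 | 3.49 |
| 20 rating 3.8 | 32 rating 2.5 | 3.60 | 3.43 | 3.00 |
| 49 rating 4.0 | 5 rating 2.0 | 3.95 | 3.95 | 3.81 |

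The first row uses the plan's expected 84% starting (54 of 64) and its expected mean of 3.7 for finishers. There the excess over the per-patient mean is 0.30 (module means) or 0.27 (pooled), about the whole 0.3 margin. In the second and fourth rows all three versions pass, so the weighting does not change the decision.

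**Later stopping.** If the 26 dissatisfied patients of the main example stop after module 2 instead, M = (3.30 + 3.30 + 4.0 + 4.0)/4 = 3.65 and R = (2 × 171.6 + 2 × 104)/(104 + 52) = 551.2/156 = 3.53, still against 3.30 per patient.

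**Stopping unrelated to satisfaction.** If 13 of the patients rating 4.0 and 13 of those rating 2.6 stop after module 1, the later module means are (13 × 4.0 + 13 × 2.6)/26 = 3.30. All three versions then equal 3.30 and there is no distortion.

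**The case against.** The strongest reply is that the article leaves the estimator open and does not fix a biased one. Averaging within each patient first, then across patients, is compatible with its wording, and a statistical analysis plan that is not shown may say exactly that. The phrase "calculated after completion of each of the four modules) exceeds 3.4" could even be taken to require each module's mean to pass, in which case the module 1 mean of 3.30 in the main example would fail. This stands, and it limits the point to a primary pass rule whose outcome depends on an unstated choice. It does not remove the point: the article fixes the cut-off and describes module means followed by an overall mean, which most naturally reads as the mean of module means.

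A reader might also infer that dissatisfied patients vanish from the average. The documents do not support that. A patient who stops after module 1 still counts in the module 1 mean; only those who complete no module give no module rating at all. Such patients would drop out only if the analysis were restricted to four-module completers, which the article does not say.

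The direction of the effect is an assumption too. Consent and baseline fall 5–21 days before surgery, and the modules should be done by the day before, so some patients will stop for lack of time. The article itself considers a sensitivity analysis on time to surgery for criterion 2.

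Finally, there are partial safeguards. Module means are presented per arm, and missing counts are described for baseline variables, with primary outcomes to be analysed in the same way. The CSQ-I does not depend on finishing a given module. These would help a careful reader see the pattern, but none enters the >3.4 rule.

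**Conclusion.** The point holds in a limited form. Criterion 3 states neither denominator nor weighting for a mean built from ratings that exist only for completed modules. Under the module-mean or pooled reading, finishers weigh more than early stoppers, and the rule can pass when the per-patient mean does not.

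In the main example the excess is 3.825 − 3.30 = 0.53 (module means) or 3.72 − 3.30 = 0.42 (pooled), against a planned margin of 0.3. These sizes rest on assumed ratings, an assumed stopping share and a full link between dissatisfaction and stopping. With few stoppers the decision does not change, and with no such link there is no bias.

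It would go too far to conclude that the planned summary is biased, or that the typical user would not have accepted the intervention. In the main example half the starters rate 4.0, and the per-patient mean of 3.30 lies above the neutral value of 3.

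**What to change.** State the estimator in criterion 3. For each patient, average over the modules that patient rated. Then average these values across all patients in the arm who rated at least one module, and base the >3.4 decision on that mean, given with a 95% CI. Keep the module means, but show the number of raters beside each one, and report module 1 ratings separately for later stoppers and finishers. That last comparison shows whether stopping was in fact linked to dissatisfaction.

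A sensitivity analysis for randomised patients with no rating is optional. A neutral 3 is only one possible value. With 54 of 64 starting and an assumed starter mean of 3.5, giving the other 10 a 3 yields (54 × 3.5 + 10 × 3)/64 = 3.42; giving them a 2 yields 3.27.

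The cost is wording only, with no new data or visits. The reported mean may be slightly lower, by an amount that depends on how many patients stop and how they rated.

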### Sample size and study power

This feasibility study will explore the rate of completing at least one online module before surgery (outcome criterion 2). This will provide valuable information on what can be expected in a future Phase III trial. As one proportion, CIs are used to estimate a population proportion, sample size calculation is based on a CI approach. For a future Phase III trial, we want to assure that at least 75% of the patients in an iEXPECT group will complete at least one online module before surgery. In our study, we expect a completion rate of 84% in each intervention group, because it provides a meaningful buffer above the 75% feasibility threshold and ensures that the lower bound of the 95% CI will remain above this criterion, while keeping the required sample size feasible. Using a two-sided 95% CI with a lower CI limit of 75%, and an expected completion rate of 84%, we found that each intervention group should have at least 64 patients for the study. As the primary focus lies on assessing the feasibility of the online interventions, the calculated sample size is required for each of the two intervention groups. Since this is a feasibility trial and not designed to detect statistically significant differences between groups, we decided to allocate only half as many participants (N=32) to the SOC group. We consider this sample size sufficient to provide preliminary insights into secondary outcomes within the SOC group. Accordingly, patients will be randomised in a 2:2:1 ratio across the two intervention arms (iEXPECT enhanced: iEXPECT limited) and the SOC arm, resulting in a total sample size of N=160. The sample size calculation was performed using PASS V.14 software (NCSS; www.ncss.com).

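### The sample-size section says an expected 84% completion rate guarantees a lower 95% limit above 75%, but with 64 per arm and a true 84% this happens only about 55% of the time per arm

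*Protocol article*

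**What the plan says.** Under Sample size and study power, the Protocol article bases the sample size on a confidence interval for one proportion: the share of patients in an iEXPECT arm who complete at least one online module before surgery. It states "we expect a completion rate of 84% in each intervention group". The reasons given are that 84% leaves a buffer over the 75% threshold, that it "ensures that the lower bound of the 95% CI will remain above this criterion", and that the resulting sample size stays feasible. From a two-sided 95% interval with its lower limit at 75%, the section concludes "we found that each intervention group should have at least 64 patients for the study", and adds that "the calculated sample size is required for each of the two intervention groups". It gives no probability of reaching the lower limit and does not name the interval method.

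The Data analysis plan section defines the criterion itself, counting modules done preoperatively: "Feasibility of the internet-based intervention is assumed if >75% of the randomised patients in each iEXPECT arm complete at least 1 (>0) online module". On reporting it says: "The completion rate will be reported as a point estimate per intervention group, and two-sided 95% CIs will be provided". It does not require the lower limit to exceed 75%.

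**The concern.** Choosing n so that the lower limit equals the threshold when the observed rate equals the expected rate leaves no allowance for sampling variation. The observed rate will fall below the expected rate in roughly half of trials, and the lower limit then falls below 75%. A calculation of this kind cannot guarantee the lower limit.

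This matters because the claim is part of the stated justification for 64 per arm, and so for N=160, on a primary feasibility outcome meant to inform a Phase III trial. The intervals will be published. A reader who took the guarantee at face value could see a lower limit of, say, 73.6% as evidence against the intervention, although that result is quite likely when the true rate is exactly as planned.

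**Working it through.** **Inputs.** Expected rate p = 0.84, target lower limit p0 = 0.75, two-sided 95% (z = 1.96) and n = 64 per arm, all from Sample size and study power. The criterion of more than 75% in each arm comes from the Data analysis plan section.

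**1. Reproduce the plan's figure.** Wald interval: n = z² p(1−p)/(p−p0)² = 1.96² × 0.84 × 0.16 / 0.09² = 63.74, rounded up to 64. The stated figure is reproduced.

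**2. Margin at the planned rate.** Half-width at n = 64: 1.96 × √(0.84 × 0.16/64) = 0.0898, about 9 points. Lower limit: 0.84 − 0.0898 = 0.7502. The margin over 75% is 0.02 points.

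**3. Smallest count that clears 75% (Wald).**
- 53/64 = 82.8%: lower limit 0.7357, below.
- 54/64 = 84.4%: lower limit 0.7548, above.

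At least 54 completers of 64 are needed, so one patient decides the result.

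**4. Probability of clearing 75%.** With X ~ Binomial(64, p), P(X ≥ 54) gives the chance per arm. Its square gives the chance for both arms, if they are independent and share the same true rate. The table adds two other common intervals.

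| Interval | Lower limit at 84% | Needed of 64 | True 84%: one arm / both | True 90%: one arm / both |
|---|---|---|---|---|
| Wald | 75.0% | 54 | 0.551 / 0.303 | 0.948 / 0.900 |
| Wilson | 73.1% | 55 | 0.415 / 0.172 | 0.897 / 0.805 |
| Clopper-Pearson (exact) | 72.7% | 56 | 0.285 / 0.081 | 0.813 / 0.662 |

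Wald, the method that yields 64, is the most favourable of the three.

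**5. Criterion 2 as the Data analysis plan words it.** More than 75% of 64 means at least 49, because 48/64 is exactly 75%.
- True 84%: P(X ≥ 49) = 0.958 per arm, and 0.958² = 0.918 for both.
- True 75%: P(X ≥ 49) = 0.452 per arm.

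The two readings of the same threshold therefore behave very differently at the planned rate: 96% against 55% per arm.

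**The case against.** The strongest reply is that nothing in the trial depends on the lower limit. Criterion 2 is written as a proportion of patients, the interval is only reported beside it, and on that criterion a true 84% passes in both arms about 92% of the time. This stands. A reader might infer from the 55% and 30% figures that the feasibility decision is close to a coin flip. The documents do not support that, because no section makes the lower limit a pass/fail rule.

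A second reply is that sizing on an interval at the expected rate is a recognised precision method for a feasibility study, that the section claims no power, and that the verb *ensures* merely describes how 84% relates to n. The first two parts stand: the method is legitimate and 64 is arithmetically correct. The third does not. The sentence says where the bound will lie, and at a true 84% it will not lie there in about 45% of arms (1 − 0.551).

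Third, the section frames its aim per group and never claims that both lower limits will clear 75% together. That is fair. The 30% is a derived figure, relevant because two arms are sized this way and the criterion applies to each; the per-arm 55% carries the point.

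Fourth, the Wilson and exact figures might be read as showing that 64 is wrong. They do not. The section names no interval and 64 fits Wald. These figures show only how far the claim depends on the interval chosen.

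**Conclusion.** The concern holds as a misstated design property. With 64 per arm and a true completion rate of 84%, the Wald lower limit exceeds 75% with probability about 55% per arm and about 30% for both, and other standard intervals give less. The claimed guarantee is therefore false under the plan's own assumptions.

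The point does not show an error in n = 64, a trial that is too small for its purpose, or a probable failure of criterion 2. What remains open is a mismatch: the arms are sized on the lower limit, while the criterion is worded on the observed proportion. On that wording a planned 84% is very likely to pass, but a true rate of exactly 75% also passes about 45% of the time per arm.

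The figures assume binomial counts, all 64 randomised patients per arm in the denominator, the same true rate in both arms and, for joint figures, independent arms. Severity: should be fixed. It changes a stated property, with no effect on sample size or analysis.

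**What to change.** Keep N=160 and revise the wording.

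1. Delete *ensures* and call 84% a planning assumption. The section supports it only by the buffer it leaves and the sample size it allows.
2. State what the design delivers: 64 per arm gives a 95% interval of about ±9 points at 84%. The probability that the Wald lower limit exceeds 75% is about 55% per arm (30% for both) at a true 84%, and about 95% (90% for both) at a true 90%.
3. If the analysis will use another interval, quote that interval's own figures. For Wilson these are 41% and 17% at a true 84%, and 90% and 80% at a true 90%.
4. State that criterion 2 is judged on the point estimate, as the Data analysis plan reads, or change it explicitly to the lower limit. Give the matching pass probability: 96% per arm and 92% for both on the point estimate at a true 84%, with 45% per arm at a true 75%; or the lower-limit figures above.

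The cost is a few sentences and no extra patients. The stated property becomes less favourable.

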### Data monitoring

To ensure confidentiality, all study data will be deidentified using a unique coding system (e.g., first patient in Marburg ‘176-001’), with personal identifiers replaced by anonymised codes. Only study investigators will have access to the coded dataset. Results will be published exclusively in anonymised form. As part of quality assurance, a random sample of entries will undergo source document verification; for example, surgical dates in REDCap will be cross-checked against patient medical records to confirm accuracy. The study management team maintains a subject identification list within REDCap, enabling targeted verification in collaboration with clinical sites. While the study is ongoing, access to the data is strictly limited to the investigators, and all output will comply with the Consolidated Standards of Reporting Trials 2025 Statement guidelines. Data analysis and manuscript preparation will be carried out jointly by the study statisticians and investigators, followed by submission to peer-reviewed journals and presentation at international conferences. Participants may request study results following their involvement.

### The Independent Data Monitoring Committee

The Independent Data Monitoring Committee (IDMC), comprising two experts in medical psychology and e-mental health interventions, is responsible for independently evaluating patient safety in the clinical trial. The IDMC receives regular updates in case of serious adverse events, including suicide attempts or suicides, and addresses safety concerns. It conducts regular assessments of data integrity and validity, monitors the overall conduct of the clinical trial and provides recommendations. Importantly, IDMC members operate independently from the coordinating investigators and participating centres. As this study is a feasibility trial with a smaller sample size and no dedicated funding for an IDMC, two members were deemed sufficient for the committee, compared with three in the larger PSY-HEART-II trial.^57^ While the inclusion of clinical trialists, statisticians and consumer representatives is planned for the subsequent full-scale study, the current IDMC ensures appropriate methodological and clinical oversight within the scope and resource constraints of this preliminary phase.

### Patient and public involvement

While there was no formal patient and public involvement (PPI) in the design, conduct or dissemination of the iHEART trial, patient perspectives were indirectly integrated through prior studies, clinical experience and close collaboration with cardiac surgeons. The iEXPECT intervention builds on earlier face-to-face formats, which incorporated patient feedback—such as increasing the number of booster sessions and undergoing pilot testing with patient volunteers. However, an important aspect of the current iHEART trial is to gather patient feedback on the acceptability of specific intervention modules, which will directly inform the refinement and optimisation of the intervention in a subsequent full-scale Phase III trial. For future studies, we intend to explicitly incorporate PPI, drawing on the quantitative and qualitative findings from the iHEART trial and potentially involving organisations such as the German Heart Foundation to support and guide the development process more systematically.

